## Abstract

Cardiovascular diseases (CVDs) comprise 45% of all deaths in Europe and causes 3.9 million deaths annually. Coronary artery disease (CAD) which includes myocardial infarction (MI) represents the most common form of CVD. A relevant proportion of MI cases seems preventable since reports claim that up to two-thirds of these patients exhibit symptoms suggestive for MI within 12 months prior to the acute MI event. An early identification of these at-risk subjects is necessary to manage an early and efficient treatment during the ischemic phase. The aim of the PRecision MEDicine in Coronary Artery Disease (PREMED-CAD) consortium is to apply a system medicine approach towards studying and identifying an ischemia specific ‘biomarker signature’ that improves the identification of individuals ‘at-risk’ for acute MI. The consortium will take an interdisciplinary and translational approach integrating knowledge from CAD epidemiology, imaging, bioinformatics, statistics and molecular biology, as well as existing phenotypic, blood-based and clinical biomarker data of distinct CAD and subclinical MI phenotypes. This biomarker signature will be validated through atherosclerosis-prone mouse models and human cohorts. The validated signature will be translated in a real-world clinical setting using an ongoing clinical trial comprising patients with subclinical ischemia. The aim of the knowledge obtained from this project is to aid in early MI detection and reduce the mortality and morbidity rate in these at-risk MI individuals.

## 1. Introduction

Cardiovascular disease (CVD) causes more deaths among Europeans than any other disease condition [1]. According to Global Burden of Disease database, there was an incidence of 6 million of individuals suffering acute coronary syndrome (ACS) in Europe in 2015. CVD is among the leading causes of death in Europe and the World Health Organization (WHO) has stated that 80% of the deaths are due to premature heart diseases are preventable with intervention at the correct time. It is estimated that up to two-thirds of these individuals consulted at the emergency room (ER), a specialized chest pain unit (CPU), or the general practitioner within 12 months prior to the acute event with symptoms suggestive for myocardial ischemia. Thus, an early identification is required for these at-risk subjects <12 month prior to the disease occurrence, in order to significantly reduce morbidity, mortality, and the burden on health and socioeconomic status.

Existing clinical tools to identify the initial (subclinical) stages of CVD include electrocardiography (ECG), echocardiography, measurement of troponin, magnetic resonance imaging (MRI), and elective coronary angiography. These tools often fail to take into consideration the myriad of risk factors associated to CVD that would aid in providing a timely intervention. As evidenced by data from the American National Cardiovascular Data Registry, elective coronary angiography shows low diagnostic yield [2]. Out of a total of 398,978 patients undergoing coronary angiography, only 37.6% had an obstructive CAD [2]. Moreover, in this registry, non-invasive tests like ECG, ergometry, and stress echocardiography showed no incremental value. Despite the well-established knowledge on CVD risk factors, current existing tools fail to adequately identify subjects prior to MI event. Recently, in order to improve the risk estimation of CAD, much attention has been given to the potential of circulating, blood-based biomarkers. Multiple studies evaluated the predictive value of biomarkers reflecting hemodynamics, micronecrosis, inflammation, lipids, neuro-humoral activity, and renal function beyond the classical risk factor models. In particular, the strongest additional predictive value has been shown for natriuretic peptides (NPs), high sensitivity assayed troponin (hs-Tn), and C-reactive protein (CRP). NPs are synthesized in response to cardiac wall stress in association with volume overload [3], while, troponin levels are usually increased because of cardiomyocyte necrosis [4]. CRP is a sensitive but a non-specific marker of inflammation which positively correlates with CVD incidence [5] and mortality [6].

## 2. Unmet Need and Rationale of PREMED-CAD

Within PREMED-CAD, a biomarker signature for ischemia prior to MI event will be derived using bioinformatics tools and its validation in animal models and human disease cohorts. In the final step, the validated biomarker signature will be translated into the ongoing clinical trial GRAY-ZONE to evaluate the clinical applicability of the biomarker signature for the early identification of at-risk subjects for ischemic coronary events. The aim of the PREMED-CAD consortium is to find biomarkers that have the ability to identify patients that are at-risk (<12 months) of developing MI. The groundwork of PREMED-CAD relies on an already existing extensive set of biomarkers, epidemiological cohorts with deep phenotyping and imaging data, biomaterials, and distinguished animal models. The target population are at-risk MI patients that show inconclusive symptoms of CAD and within whom diagnostic and therapeutic measures fall short.

## 3. Design and Methodology

### 3.1. Design

The PREMED-CAD consortium comprises of three participating partner institutions in Europe, the University Medical Center, Hamburg (Hamburg, Germany), INSERM Bordeaux (Bordeaux, France) and IRCCS San Raffaele Pisana (Rome, Italy). The partner institute in Hamburg is one of the largest German University hospital treating +20,000 CVD patients per year. Therefore, within this consortium, access to clinical cohorts will be provided by the German partner. The Italian partner holds extensive experience with animal models of atherogenesis and atherosclerosis and aims to validate and consolidate findings of the human cohorts. The French partner provides computational infrastructure and statistical and bioinformatical expertise to identify a concise risk signature out of the vast data available and being generated. All partners hold deep understanding and high-level expertise on the fundamentals and the characteristics of CVD and underlying atherosclerosis. Each participating institution contributes specific experience, materials and methods that enable a systemic investigation of CVD mechanisms leading to a validated biomarker signature that improves early MI at-risk detection. The diversity of expertise ranges from computational to clinical-molecular and molecular-physiological knowledge. A large spectrum of molecular biology and human resources along with the ability to translate the final biomarker signature through a clinical trial will result in the maximal use of all available data.

Within PREMED-CAD, a biomarker signature specific to ischemia will be derived (Figure 1). For this purpose, deep-phenotyping data, blood biobank and cardiac stress-MRI test are available for at-risk MI patients from the IMAGING cohort, *n* = 200 (signature derivation cohort) and Stress-T1 cohort, *n* = 200 (signature validation cohort). The derived ischemia specific biomarker signature will be compared to patients without ischemia within the IMAGING and Stress-T1 cohort. Additional validation will be performed in ischemia animal models and optionally in the large population-based study—the Hamburg City Health Study (400 ischemia-MRIs). Ultimately, the validated biomarker signature will be translated in an ongoing clinical trial GRAY-ZONE to evaluate the clinical applicability of the biomarker signature for the early identification of at-risk subjects for ischemic coronary events.

### 3.2. Methodology

#### 3.2.1. Derivation of the Optimal Biomarker Signature

Derivation of first minimal consensus biomarker signature will be performed in the IMAGING cohort data by capitalising on already identified candidate biomarkers (including miRNAs, troponin, natriuretic peptides, C-reactive protein (CRP) and metabolites). The disease signature will be derived when the data from the diseased cohort is compared to healthy individuals. For the analysis, we will apply generalised additive models [7] coupled with backward selection procedures to identify the most relevant linear and non-linear predictors of CVD. Discriminative performances and adjustment for optimism will be performed on each cohort. Subsequently, different correlation networks [8], unsupervised clustering and machine/deep learning methodologies [9,10,11] will be applied to identify new biological partners to these candidates. These data will also be integrated into knowledge-based biological databases such as KEGG, Reactome, Gene Ontology database and other publicly available “omics” resources. In the final step, identified markers will be combined to determine an optimal biomarker signature between performance of the prediction model and clinical usefulness. Regression coefficients from the multivariate regression models will be transformed into the components of a risk score. Sensitivity, specificity, positive predictive value (PPV) and negative predictive value (NPV) for several cut-off scores will be calculated.

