In parallel to the validation of the biomarker signatures in murine models, additional epidemiological cohorts (Stress-T1, population-based cohort) will serve for independent validation and biomarkers will be measured. For this, serum/plasma samples from patients with early ischemia i.e., Stress-T1 cohort bio-bank will be used. Similar to the IMAGING cohort, Stress-T1 is a cardiac stress-MRI cohort that was specifically designed in order to find new blood-based biomarkers predicting myocardial ischemia. Both cohorts share the same inclusion criteria (age above 18 years, patients capable of giving informed consent, clinical indication for routine cardiac stress-MRI), and exclusion-criteria (acute myocardial infarction, known untreated coronary heart disease, known myocardial ischemia as assessed by stress-echo, scintigraphy, or similar procedures).

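### Section 3.2.1 derives the signature against healthy individuals, but the derivation cohort holds only patients referred for stress-MRI and Section 3.1 names non-ischemic patients as the comparator

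*Protocol article*

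**What the plan says.** Section 3.2.1 gives both the data source and the contrast. On the source: "Derivation of first minimal consensus biomarker signature will be performed in the IMAGING cohort data". On the contrast: "The disease signature will be derived when the data from the diseased cohort is compared to healthy individuals". The section ends with the accuracy measures: "Sensitivity, specificity, positive predictive value (PPV) and negative predictive value (NPV) for several cut-off scores will be calculated".

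Section 3.1 assigns IMAGING (n = 200) to derivation and Stress-T1 (n = 200) to validation, and names a different comparator: "The derived ischemia specific biomarker signature will be compared to patients without ischemia within the IMAGING and Stress-T1 cohort".

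Section 3.2.2 gives entry criteria shared by both cohorts, among them a "clinical indication for routine cardiac stress-MRI". Ischemia already known from other tests is an exclusion. The same paragraph describes the validation material thus: "serum/plasma samples from patients with early ischemia i.e., Stress-T1 cohort bio-bank will be used".

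Section 2 states the intended use: "The target population are at-risk MI patients that show inconclusive symptoms of CAD".

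**The concern.** The clinical question is which symptomatic patients with unclear findings are ischemic. Healthy people differ from ischemic patients in more than ischemia: they have not been referred, and they may carry fewer risk factors and less general illness. A selection procedure run on that contrast can keep markers of those other differences. CRP shows the problem: it is a listed candidate in Section 3.2.1, and the Introduction itself describes it as non-specific.

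Accuracy measured against such controls would look better than in the target population, and a cut-off placed to spare healthy people would sit too low for referred patients. The optimism adjustment in Section 3.2.1 deals with overfitting, not with the choice of controls. Section 5 says that a weak signature endangers every later step, and Section 4 intends to use the signature to label GRAY-ZONE patients positive or negative. All of those patients have chest pain and raised troponin, so they do not resemble healthy controls.

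**Working it through.** **Step 1: set the statements side by side.**

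| Item | Where | Content |
|---|---|---|
| Derivation data | 3.2.1 | IMAGING |
| Derivation contrast | 3.2.1 | diseased cohort against healthy individuals |
| Comparator | 3.1 | non-ischemic patients in IMAGING and Stress-T1 |
| Who enters both cohorts | 3.2.2 | patients referred for stress-MRI |
| Intended population | 2 | at-risk patients with inconclusive symptoms |

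No healthy group is described in IMAGING. The first two rows are therefore compatible only if the healthy individuals come from a source that is not named, or if the word means IMAGING patients without ischemia. The article does not say which.

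**Step 2: is there a figure to reproduce?** No. The article states no AUC, specificity, power or sample-size calculation for the signature, and no split of either cohort by ischemia.

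**Step 3: illustration.** All inputs here are assumptions: a normally distributed score with unit SD in each group; a true AUC of 0.65 for ischemic against non-ischemic referred patients; healthy people lying h SD below the non-ischemic patients, with h from 0 to 1.0; and a cut-off giving 90% specificity in whichever controls are used for derivation.

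- Separation of ischemic from non-ischemic patients: d = √2 × Φ⁻¹(0.65) = 0.545.
- Apparent AUC against healthy controls: Φ((0.545 + h)/√2).
- Cut-off, measured from the non-ischemic mean: 1.282 − h. Specificity in non-ischemic referred patients: Φ(1.282 − h).

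| h (SD) | Apparent AUC | Specificity in referred non-ischemic patients |
|---|---|---|
| 0 | 0.650 | 90.0% |
| 0.5 | 0.770 | 78.3% |
| 1.0 | 0.863 | 61.1% |

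**Step 4: sensitivity to the assumed separation.** With d = 0.3, 0.5 and 0.8, the AUC against non-ischemic patients, Φ(d/√2), is 0.584, 0.638 and 0.714. Against healthy controls 0.5 SD lower it is 0.714, 0.760 and 0.821; at 1.0 SD lower it is 0.821, 0.856 and 0.898. The specificity column does not depend on d. The apparent AUC is too high whenever healthy people score lower than non-ischemic referred patients; with h = 0 there is no inflation.

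**The case against.** The strongest reply is that the sentence is loosely worded. Section 3.2.1 has just placed derivation in IMAGING, no outside control group is named, and healthy may simply mean non-ischemic IMAGING patients. That reading is reasonable and removes the inflation. It is not secure, because the sentence sets a diseased cohort against healthy people rather than two groups within one cohort, and the section speaks of a disease signature and predictors of CVD where Section 3.1 speaks of ischemia.

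Second, the Section 3.1 sentence refers to a signature already derived, so it may describe a later step. The two sections would then not strictly contradict each other, and an ischemic against non-ischemic comparison would already be planned. This stands, but it leaves Section 3.2.1 as the only statement of the derivation contrast.

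Third, the healthy contrast is attached to a first minimal signature. Further steps and a final combination follow, then Stress-T1, optionally a population-based cohort, and GRAY-ZONE with 12-month events. These are real safeguards. They can show that a signature performs poorly, but they do not reselect its markers.

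Fourth, the article condenses a fuller protocol. An omitted control definition would be no finding. Here, however, a comparator is stated, and it does not fit the cohort named beside it.

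**Conclusion.** The derivation comparator is badly fixed and should be settled before derivation. Whether this means bias or only wrong wording depends on what healthy individuals means. Taken literally, the derivation contrast does not match the target population, and marker selection, AUC, specificity and cut-offs at that stage are affected. Taken loosely, only the text is at fault. The size is not determinable from the documents; the range of 0.65 to 0.86 for a true AUC of 0.65 rests wholly on the assumed 0 to 1.0 SD shift.

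Two stronger readings are not supported. A reader might infer that the signature's accuracy will be inflated. The documents support this only conditionally, since no healthy control source is named and the planned checks in Stress-T1 and GRAY-ZONE use other patients. A reader might also infer from the early-ischemia label that the Stress-T1 validation set contains cases only, so that specificity, predictive values and AUC cannot be estimated there. Section 3.1 places non-ischemic patients in that cohort, and the Section 3.2.2 criteria admit patients referred for stress-MRI whatever its result. The label is loose wording and does not describe the composition of the cohort.

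**What to change.** Reword the derivation sentence in Section 3.2.1 along these lines: *The signature is derived in IMAGING by comparing patients with and without ischemia on stress-MRI, and is validated on the same contrast in all Stress-T1 patients.*

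In Section 3.2.2, replace the early-ischemia label with a statement that samples from all Stress-T1 patients are measured, with or without ischemia.

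If a healthy-control comparison is wanted, name its source and keep it descriptive: it should not enter marker selection, cut-offs, sensitivity, specificity, PPV or NPV.

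If done before derivation, the cost is a change of wording, since Section 3.1 says that biobank samples and stress-MRI are available for both cohorts. There are two downsides. Reported accuracy may look less favourable. The controls for derivation are also limited to the non-ischemic patients among the 200 in IMAGING, a number the article does not give. If a signature has already been derived against healthy people, it would have to be derived again.

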#### 3.2.2. Validation of Biomarker Signature

To validate the biomarker signatures derived from bioinformatics analyses, independent measurements will be performed in experimentally characterized murine models as well as in independent human epidemiological cohort. This will help to better understand the dynamics of our identified biomarker signature since we evaluate it in disease models mirroring the transformation from healthy stage to disease stage.

Characterisation in experimental murine models will be performed in apolipoprotein E-deficient knockout (ApoE-/-) mice. A remarkable body of evidence has shown that ApoE-/- mice represent a suitable animal model to study mechanisms underlying the atherosclerosis process. In addition, treatment of such mice with aldosterone allows to study vascular alterations occurring in atherosclerosis [12,13]. The influence of aldosterone + proatherogenic high fat diet (HFD) will be compared to aldosterone + western diet in both ApoE-/- mice and wild-type mice (i.e., four groups, each *n* = 10 female and male). In these four groups, the spectrum of atherosclerosis progression (from ischemia to MI) will be achieved by occlusion of the left anterior descending (LAD) since LAD ligation represents a valuable experimental model of MI and ischemia (Figure 2).

Therefore, the mice will be subjected to different conditions that accurately represent the dynamics of progression of CAD prior to MI. LAD occlusion will be performed for different time periods such as 20 min, 6 h, 24 h and 6 weeks. Such a model is suitable to obtain a broader overview of the difference in signature prior to the MI event and validate very early markers of acute MI before the occurrence of tissue necrosis [14]. To address the gender issue, both female and male mice (*n* = 15 in each group) with ApoE-/- will be chosen, since ApoE-/- male mice develop an atherosclerotic plaque within 4–8 weeks of aldosterone treatment and concomitant feeding with proatherogenic HFD, whereas the female mice develop increased plaque development even in the absence of aldosterone treatment. Samples are collected to allow for measurement of biomarkers. All animal experiments are approved by the Italian National Institutes of Health Care and Use Committees, Rome, Italy (493/2016-PR, 05/17/2016, [name], MD, Ph.D)

In parallel to the validation of the biomarker signatures in murine models, additional epidemiological cohorts (Stress-T1, population-based cohort) will serve for independent validation and biomarkers will be measured. For this, serum/plasma samples from patients with early ischemia i.e., Stress-T1 cohort bio-bank will be used. Similar to the IMAGING cohort, Stress-T1 is a cardiac stress-MRI cohort that was specifically designed in order to find new blood-based biomarkers predicting myocardial ischemia. Both cohorts share the same inclusion criteria (age above 18 years, patients capable of giving informed consent, clinical indication for routine cardiac stress-MRI), and exclusion-criteria (acute myocardial infarction, known untreated coronary heart disease, known myocardial ischemia as assessed by stress-echo, scintigraphy, or similar procedures).

## 4. Translational Aspect—GRAY-ZONE

The current literature shows that in patients presenting with chest pain, high-sensitive troponin levels above the 99th percentile are indicative for future cardiovascular events, even when acute coronary syndrome was ruled out. Most of these non-ACS-patients are discharged without specific/ preventive therapy (anti-platelet or anti-lipid), although ‘positive’ troponin values (any value at any time during hospitalization above the 99th percentile) seem to clearly indicate underlying myocardial ischemia. In summary, there is an unmet need with a huge potential to reduce mortality and morbidity in ER patients by specific therapy. GRAY-ZONE is an ongoing clinical trial, fully financed by the German Research Foundation, and initiated by the German partner. A total of 3000 troponin positive patients presenting at ER/ CPU with acute chest pain, but ruled-out ACS, will be assigned randomly to Aspirin and/ or Atorvastatin versus placebo (2 × 2 factorial design). The primary endpoint is a composite of non-fatal stroke, non-fatal MI and cardiovascular death. The final biomarker signature, which will be derived within the PREMED-CAD project will be translated and validated retrospectively in GRAY-ZONE. Therefore, we will be able to assess whether this signature is capable of predicting those subjects developing a clinical ischemic event during the 12-months follow-up. Bio-banking in the GRAY-ZONE trial is available at baseline and at 12-months follow-up. This will allow us to investigate the dynamics within the identified biomarkers and final biomarker signature; and also in the clinical event rate in PREMED-CAD-biomarker positive versus PREMED-CAD-biomarker negative patients of the three active, well-tolerated therapies (Aspirin, Atorvastatin, Aspirin combined with Atorvastatin). This project directly paves the way to personalized and biomarker-guided therapy.

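### Troponin is both a candidate signature component and the GRAY-ZONE entry criterion, and the article names only stand-alone accuracy measures for a signature meant to improve identification

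*Protocol article*

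**What the plan says.** All references are to the protocol article.

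- **Aim.** The Abstract and section 3.1 describe a signature that improves the identification or early detection of people at risk of MI.
- **Existing markers.** Section 1 reports that, beyond classical risk factor models, "the strongest additional predictive value has been shown for natriuretic peptides (NPs), high sensitivity assayed troponin (hs-Tn), and C-reactive protein (CRP").
- **Derivation.** Section 3.2.1: "Derivation of first minimal consensus biomarker signature will be performed in the IMAGING cohort data", starting from "already identified candidate biomarkers (including miRNAs, troponin, natriuretic peptides, C-reactive protein (CRP) and metabolites"). Backward selection follows, then a search for further markers.
- **Performance.** Section 3.2.1 names discrimination with adjustment for optimism in each cohort, and then "Sensitivity, specificity, positive predictive value (PPV) and negative predictive value (NPV) for several cut-off scores will be calculated". No cut-off is fixed there.
- **Entry to IMAGING and Stress-T1.** Section 3.2.2 requires adulthood, consent and a "clinical indication for routine cardiac stress-MRI". It excludes acute MI, known untreated coronary heart disease and known ischemia. There is no troponin criterion.
- **GRAY-ZONE.** Section 4 enrols "A total of 3000 troponin positive patients presenting at ER/ CPU with acute chest pain, but ruled-out ACS". It describes positive troponin as "any value at any time during hospitalization above the 99th percentile". The final signature is validated there retrospectively against events over 12 months, and event rates are compared between biomarker-positive and biomarker-negative patients.

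**The concern.** Two features of the design meet in GRAY-ZONE.

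First, a marker that may carry weight in the score also decides who enters. Selecting patients on one component of a score narrows that component's spread and raises its mean. Discrimination then falls through selection alone, and a fixed score threshold labels a larger share of patients positive. A sound signature could look weak in GRAY-ZONE for this reason. Section 5 warns that a weak signature endangers the later steps, but does not mention this possibility. The positive/negative comparison in section 4 needs a threshold, and the article does not say where it comes from.

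Second, improvement is a comparative claim. Discrimination, sensitivity, specificity, PPV and NPV of the signature taken alone cannot show that it adds to hs-troponin, natriuretic peptides and CRP, which the article itself ranks highest. A signature could do well in every cohort because it contains those markers and still add nothing to them. In GRAY-ZONE every patient already has a troponin result, so value beyond troponin is the relevant question.

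**Working it through.** The article gives no AUC, cut-off or event rate for the signature, so there is no figure to reproduce. The calculation below only indicates scale.

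**Inputs from the article:** GRAY-ZONE is restricted to troponin-positive patients (section 4); IMAGING is not restricted on troponin (section 3.2.2); troponin is a candidate component (section 3.2.1).

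**Assumed inputs (not in the article):**
- Score S = 1.2 × (√w·Z + √(1−w)·M), where Z is standard-normal log-troponin and M an independent standard-normal component for all other markers.
- w, the share of score variance due to troponin: 25%, 50% or 75%.
- Outcome risk = 1/(1 + exp(3 − S)), the same in both populations.
- q, the share of the derivation population above the troponin threshold: 5% to 50%.
- GRAY-ZONE taken as Z > t, with t the 1−q normal quantile (strict truncation).

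**Share positive at a transported cut-off.** Take a cut-off marking the top 25% in derivation, c = 0.674 SD. Among troponin-positive patients the share positive is P(S/1.2 > c and Z > t)/q, from a bivariate normal with correlation √w. For w = 0.5 and q = 0.10: correlation 0.707, t = 1.282, joint probability 0.077, so 0.077/0.10 = 0.77.

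**Simulation, 2,000,000 draws per row.** AUC in the unrestricted population is 0.79 in every row. Specificity is for a cut-off with 90% specificity in derivation.

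| w | q | Score AUC, troponin-positive | Troponin alone, all → positive | Share positive (25% in derivation) | Specificity (90% in derivation) |
|---|---|---|---|---|---|
| 25% | 5% | 0.758 | 0.650 → 0.554 | 66% | 62% |
| 25% | 50% | 0.768 | 0.649 → 0.591 | 38% | 83% |
| 50% | 5% | 0.727 | 0.708 → 0.580 | 85% | 41% |
| 50% | 10% | 0.730 | 0.707 → 0.587 | 77% | 52% |
| 50% | 50% | 0.751 | 0.708 → 0.637 | 44% | 80% |
| 75% | 5% | 0.686 | 0.752 → 0.597 | 98% | 17% |
| 75% | 50% | 0.729 | 0.752 → 0.671 | 48% | 79% |

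The closed form reproduces the share-positive column. A repeat with a different seed gave 0.685 in place of 0.686, so the lower end rounds to 0.68 or 0.69. The AUC of the non-troponin component M is practically unchanged by the restriction (0.65 to 0.75, depending on w).

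**Bound.** For a score made of troponin only, a separate simulation of 1,000,000 subjects gave AUC 0.698 falling to 0.601 in the top 20% and 0.584 in the top 10%; 0.743 fell to 0.627 and 0.605. These are extremes for a multi-marker signature and should not be read as its expected loss.

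**Reference model.** This part needs no arithmetic. The aim (Abstract, section 3.1) is comparative, the measures in section 3.2.1 are not, and section 1 names the markers against which a comparison would be made.

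**The case against.** The case on the other side is substantial, and much of it stands.

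- **Troponin may drop out.** It is one of several candidates subject to backward selection. This stands: the range-restriction effect is conditional on its being retained with material weight.
- **Truncation may not be strict.** Positivity is any value during hospitalization, so troponin in the banked baseline sample may lie below the threshold. This stands, and the table shows the strict case.
- **A reader might infer that an IMAGING cut-off, or its PPV and NPV, will be carried into GRAY-ZONE.** The article does not say so. It fixes no cut-off and leaves biomarker-positive undefined. What can be said is that a cut-off from IMAGING, if used, would change meaning.
- **A reader might infer that no comparison is planned.** A condensed article does not support that; it supports only that none is named.
- **A reader might call the stress-MRI cohorts unselected, or the GRAY-ZONE entry criterion a mistake.** Neither holds. The cohorts are selected by indication and exclusions, and performance among troponin-positive patients is a legitimate question. Any discrimination seen there already goes beyond the dichotomous troponin result, though not beyond continuous troponin.
- **The outcome differs.** The cohorts concern ischemia on stress-MRI and GRAY-ZONE concerns 12-month events, so one outcome model for both is a simplification. This limits the numbers. It also gives a further reason to recalibrate.

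What remains is the overlap of entry criterion and candidate component, and the mismatch between a comparative aim and the stand-alone measures stated.

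**Conclusion.** The point holds in conditional form. Troponin is both a candidate component and the entry criterion of the trial in which the signature is finally tested, while the derivation and first human validation cohorts carry no troponin criterion. If troponin is retained, GRAY-ZONE discrimination cannot be set beside the derivation figure without allowing for selection. Under the stated assumptions the AUC of a mixed score falls from about 0.79 to about 0.69–0.77, and 25% positive becomes 38–98%. The direction follows from selection on a retained component, with the outcome model held equal. The size depends on troponin's weight, on the share above the threshold and on strict truncation, none of which the article gives.

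Independently of whether troponin is retained, the measures stated cannot answer whether the signature improves on existing markers. This is a change that should be made, not a flaw that invalidates the project.

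**What to change.** 1. In Stress-T1 and GRAY-ZONE, report the gain of the locked signature over a reference model of clinical risk factors plus continuous hs-troponin, natriuretic peptide and CRP: difference in AUC with 95% CI, and a likelihood-ratio test for adding the signature. Keep the stand-alone measures beside it.
2. In GRAY-ZONE, recalibrate the score to 12-month risk before classifying patients as biomarker-positive or biomarker-negative for analysis, and state the classification rule in advance. Recalibration of intercept and slope (with a positive slope) leaves the AUC unchanged. It addresses the threshold, not the range restriction.
3. Report PPV and NPV at GRAY-ZONE's own event rate.
4. If troponin is retained, add a sensitivity analysis of the score without its troponin term. This shows how much of any drop in discrimination comes from selection on that marker.
5. State that GRAY-ZONE results apply to troponin-positive patients with ACS ruled out.

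**Cost.** This is analysis wording only. The three reference markers are already candidates, and GRAY-ZONE holds baseline biobank samples. Enrolment does not change. The price is a less favourable figure, because the incremental gain will be smaller than the stand-alone accuracy. With n = 200 in Stress-T1, its interval for the gain is likely to be wide.
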